## Abstract

**Background::**

Hot flashes (HF) are a prevalent symptom associated with menopause affecting up to 85% of women aged 40 to 65 years. Previous studies indicated that acupuncture might relieve the symptom of HF significantly; however, its effectiveness has not been clarified quantitatively. Electro-press needles (EPN) is a novel acupuncture that combines a shallow tiny needle with an electrical transdermal stimulator. Either the needle or the electrical stimulator could function in the treatment. This study aims to evaluate the effectiveness of EPN in comparison with no intervention in relieving HF of perimenopausal and postmenopausal women.

**Methods/Design::**

This study will be a 2-arm randomized waitlist controlled trial. According to the ratio of 1:1 and block randomization, a total of 122 patients with moderate or severe HF will be randomly allocated to either EPN group or waitlist control group. The EPN group will receive 3 sessions of EPN treatment each week in consecutive 6 weeks, 18 sessions in total. The waitlist control group will get no intervention over the first 6 weeks. All the patients will be followed up in the next 24 weeks. The primary outcome will be the percentage of the participants whose 24-hour mean HF is 50% less than the baseline at Week 6. Secondary outcomes will include HF score, HF frequency, HF severity, the Menopause Rating Scale and Menopause-Specific Quality of Life Questionnaire Score.

**Discussion::**

This study will evaluate the effectiveness and safety of EPN treatment to alleviate HF symptoms in perimenopausal and postmenopausal women, excluding self-healing factors. The limitations of the trial design are its single-center scope, lack of placebo control and impossible to blind the acupuncturists and patients.

**Trial registration**: This clinical trial has been registered in Clinical Trial Registry (registration number: NCT04995107; date of registration: Aug 6, 2021).

## Introduction

1

Although menopause is a natural stage of women aging process, the associated symptoms, such as hot flashes (HF), night sweats, insomnia, and mood instability, negatively impact females’ quality of life and may persist for several years.^[1]^ As the most common menopause-associated symptom, HF affect up to 85% of women aged between 40 and 65 years.^[2]^ It emerges as an early indicator of cardiovascular risk, and its severity increases with the duration of the symptom.^[3]^ In China, women generally experience HF throughout their menopausal transition and menopausal period for 4 to 5 years, and some may even suffer from the symptoms as long as 12 years.^[4]^ Out of the frequent occurrence and long duration, menopause-associated HF has become the major reason that patients seek help from the perimenopausal outpatient clinics.

Hormone replacement therapy (HRT) is generally recommended to relieve menopause-associated HF.^[2]^ However, long-term usage of HRT may increase the incidence of endometrial, breast and ovarian cancer, thrombosis, and strokes.^[5]^ Complementary and alternative therapies with a better safety profile have therefore emerged in recent years,^[6]^ such as acupuncture, plant hormones, massage, and lifestyle interventions. Among those therapies, acupuncture appears popular in Europe and some other countries, but the evidence of its effectiveness in relieving HF symptom is still inconclusive.^[7,8]^

A clinical study published in 2016 revealed no statistically important difference between acupuncture and sham acupuncture (noninsertion acupuncture using blunt-tip needles) in reducing HF scores of menopausal women.^[8]^ Our previous multicenter randomized trial, conducted among 360 (180/180) women during menopause transition, indicated that the difference between the electroacupuncture group and sham electroacupuncture (minimal acupuncture at nonacupoints) was as modest as 1.2 (95% CI: 0.6–1.8, *P* = .001) in the reduction of mean 24-hours HF score after 8-week treatment.^[9]^ Nevertheless, in both of these 2 trials, the HF score reduced significantly from baseline after treatment in either acupuncture group or sham acupuncture group (reaching or approaching the clinically important difference). This controversy may arise from the following 2 reasons. First, as an integrated therapy, the effectiveness of acupuncture might be partially accounted by the placebo effects, which is especially true when treating menopause symptoms.^[10]^ Notably, the placebo effects of sham acupuncture are reported to be stronger than that of a placebo tablet.^[11]^ Second, sham acupuncture is hard to act as an inert control because either tiny acupuncture or noninsertion acupuncture using blunt-tip needles may produce certain biological effects.^[7,12]^

To clarify the controversy whether acupuncture works in treating perimenopausal and postmenopausal HF or not, this randomized controlled trial is designed to compare acupuncture intervention group against the nonintervention group. Electro Press Needle (EPN), a novel acupuncture needle combining shallow and gentle insertion with transdermal electrical stimulation, will be used in the acupuncture intervention group.

## Methods/design

2

### Trial design and setting

2.1

This study is a prospective 2-arm randomized waitlist controlled trial. It will be conducted from October 2021 to June 2023 at Guang’anmen Hospital, China Academy of Chinese Medical Sciences in China.

This trial protocol is designed in accordance with the principles of the Declaration of Helsinki and has been approved by the institutional review board of Guang’anmen Hospital. The study is designed and reported in accordance with the Standard Protocol Items: Recommendations for Interventional Trials guidelines and Standards for Reporting Interventions in Controlled Trials of Acupuncture recommendations. The flowchart of the trial is presented in Figure 1 and the outcome assessment schedule is presented in Table 1.

**Figure 1 F1:**
[figure not shown]
Flow chart of participants through the proposed trial. ∗ The Waitlist control group can receive 6 weeks EPN therapy as compensatory at weeks 7.

**Table 1 T1:** Outcome assessment schedule.

		Intervention		Follow-up	
Timepoint	Enrollment and allocation baseline week -1-0	Week 3	Week 6	Week 18	Week 30
HF dairy	X	X	X	X	X
MRS	X		X	X	X
MENQOL	X		X	X	X
Global response assessment		X	X	X	
Acceptability evaluation	X	X			
Expectance and confidence evaluation			X		
Safety evaluation of EPN			X		
Adverse events			X		
Combination of medication			X		
Adherence evaluation			X		
Completeness of research			X		

EPN = electro-press needle, HF = hot flashes, MENQOL = menopause-specific quality of life questionnaire, MRS = menopause rating scale.

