### Recruitment strategies

2.2

Patients are planned to be recruited via advertisements in websites and posters from hospitals and communities. All potentially eligible women with hot flashes will be invited to the trial, continued with a series of history taking, questionnaire, HF diary, ultrasound of uterus and ovaries, and laboratory examination to screen and enroll the patients, as recommended by ACOG guideline.^[2]^ Eligible patients will be randomly divided into EPN group and waitlist control group.

Personal information including age, marriage, menstrual, education background, and medical history are cautiously recorded. Hot flashes diaries are applied to assess the severity of HF symptoms. Menopause rating scale (MRS) and Menopause-Specific Quality of Life Questionnaire (MENQOL) are applied to assess the influence on the quality of life. Patients’ expectance and confidence evaluation toward EPN will also be evaluated before the trial. The duration of the trial is 31 weeks for each patient, including 1-week baseline assessment (week 0–1), 6-week treatment period (week 1–6), and 24-week follow-up (week 7–30).

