#### Waitlist control group

2.8.2

Patients in the waitlist control group will receive no intervention for the first 6 weeks and be followed up in the next 24 weeks. If the HF symptom of the patients in the wait list does not heal itself, 6 weeks of EPN therapy will be offered to the patients as a compensation.

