##### Secondary outcome measure

2.8.3.2

1.The proportion of patients with a reduction of 50%^[17]^ or more on the mean 24-hour HF score from baseline at weeks 3, 18, and 30.2.The proportion of patients with a reduction of 50% or more on the mean 24-hour HF frequency from baseline at weeks 3, 6, 18, and 30. The mean 24-hour HF frequency will be calculated based on the number of HF recorded in 7-day HFD, as follows: mean 24-hour HF frequency = total number of HF reported/number of days reported.3.The proportion of patients with at least a 50% reduction in the mean 24-hour HF severity from baseline at weeks 3, 6, 18, and 30. The mean 24-hour HF severity will be calculated based on the frequency of HF and the severity of each HF recorded in 7-day HFD, as follows: mean 24-hour HF severity = (1 × number of mild HF + 2 × number of moderate HF + 3 × number of severe HF + 4 × number of very severe HF)/number of HF reported.4.The changes in the mean 24-hours HF score^[17]^ from baseline at weeks 3, 6, 18, and 30. A decrease of 5.35 episodes in moderate and severe HF per day from baseline has been reported as minimal clinically important difference (MCID).^[18]^5.The changes of MRS score from baseline at weeks 6, 18, and 30. MRS is a menopause-specific subscale commonly used for Chinese women. It includes 11 items concerning psychological, somatic, and urogenital domains.^[19]^ The scores of MRS range from 0 (best) to 44 (worst), and an increase of 5 points is regarded as the MCID).^[20]^6.The changes of MENQOL score from baseline at weeks 6, 18, and 30. MENQOL is a validated measurement of the quality of life and clinical symptom changes during the menopausal transition and the first 8 years postmenopause.^[21]^ It consists of 29 items to assess the 4 domains of vasomotor symptoms, physical symptoms, psychological symptoms, and urogenital/sexual symptoms. The total score of MENQOL ranges from 0 (best) to 174 (worst), with a reduction of 4 points as MCID.^[21–22]^7.The proportion of participants reporting “significantly reduced” or “moderately reduced” based on Global Response Assessment at weeks 3, 6, 18, and 30. The responses of participants to the treatments are divided into 7 grades of Global Response Assessment: significantly reduced, moderately reduced, slightly reduced, no change, slightly aggravated, moderately aggravated, and significantly aggravated. The proportion of participants reporting “significantly reduced” or “moderately reduced” are recorded as the response rate of overall efficacy.8.Patients’ acceptability toward EPN at the end of the 1st and 9th treatments. The acceptability toward EPN will be assessed among participants in the EPN group using a 3-point index: unacceptable (0 points), acceptable (1 point), and easy to accept (2 points). Those who regard EPN unacceptable will report the reasons. The average score will be calculated after the 2 assessments.9.Expectations and confidence of patients in the EPN group at baseline. Patients in the EPN group will answer the following questions before the first intervention: “Do you think acupuncture is effective for treating the disease?” and “Do you think acupuncture is effective in alleviating menopausal associated HF?” The participants can answer “Yes,” “No,” or “Unclear.”

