### Statistical analysis

2.9

The primary outcome of 24-hour mean HF score will be compared between the EPN group and the waitlist control group at week 6. Those who did not feedback data of HF score at week 6 will be regarded as patients whose reduction does not reach 50%. A *P* value <.05 will be considered statistically significant. Subgroup analysis will be conducted among perimenopausal patients and postmenopausal patients.

Continuous data will be presented as mean ± standard deviation when normally distributed, or be presented as median (interquartile range) when not normally distributed. Categorical data will be presented as the number and percentage of participants. Statistical comparisons will be performed by Student *t* test or Wilcoxon rank sum test for continuous data and by X^2^-test or Fisher exact test for categorical data. Data will be analyzed using SPSS software V.22.0 (IBM SPSS Statistics; IBM Corp, Somers, NY).

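### Arm comparisons at weeks 18 and 30 contrast immediate EPN with delayed, optional EPN, not EPN with no intervention, because waitlist patients are offered EPN from week 7

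*Protocol article*

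**What the plan says.** The Abstract fixes the comparator: "This study aims to evaluate the effectiveness of EPN in comparison with no intervention in relieving HF of perimenopausal and postmenopausal women". The Introduction likewise sets the acupuncture group against a group without intervention.

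The waitlist arm meets that description for a limited time. Section 2.8.2 says its patients "will receive no intervention for the first 6 weeks and be followed up in the next 24 weeks", and that if the HF symptom "does not heal itself, 6 weeks of EPN therapy will be offered to the patients as a compensation". The Figure 1 legend gives the timing: "The Waitlist control group can receive 6 weeks EPN therapy as compensatory at weeks 7".

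Section 2.8.3.2 lists secondary outcomes 1 to 7 at visits that include weeks 18 and 30. Item 5 is typical: "The changes of MRS score from baseline at weeks 6, 18, and 30". None of these seven is limited to one arm. Items 8 and 9 (acceptability; expectations and confidence) are expressly limited to the EPN group.

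Section 2.9 ties the primary comparison to week 6. It then names general tests: Student t or "Wilcoxon rank sum test for continuous data", and chi-square or Fisher exact for categorical data. It sets no limit by visit and no rule for waitlist patients who have taken EPN. The limitations at the end of the Discussion cover lack of blinding and lack of placebo; the Abstract adds the single centre. Neither mentions treatment of the control arm after week 6.

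**The concern.** The aim, the waitlist rule, the outcome list and the tests do not fit together after week 6. Read as written, the plan would compare the two arms at weeks 18 and 30, when an unknown share of the control arm has been offered and may have completed the same treatment.

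The risk lies in interpretation. A small or absent difference at week 30 could be reported as an effect that has worn off, when it may only show that controls were treated. The Discussion's argument that a waitlist separates EPN from spontaneous recovery also holds only while the waitlist remains untreated.

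Dropping treated waitlist patients would not repair this. The offer goes to those still symptomatic, so the patients left would be a selected group who had recovered or declined.

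**Working it through.** **1. The plan's own figure.** Section 2.8.3.4 assumes response rates of 55% (EPN) and 28% (waitlist), 80% power and two-sided 5%. With unpooled variance:

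n = (1.960 + 0.842)² × (0.55 × 0.45 + 0.28 × 0.72) / 0.27² = 48.35, rounded up to 49 per group.

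This reproduces the stated 49. It concerns week 6, before any waitlist EPN, and is not in question.

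**2. Timing.** Six weeks from week 7 is about weeks 7 to 12.

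| Visit | Weeks since end of course, EPN arm (ends week 6) | Weeks since end of course, waitlist patient starting at week 7 |
|---|---|---|
| Week 3 | during course | not started |
| Week 6 | 0 | not started |
| Week 18 | 12 | 6 |
| Week 30 | 24 | 18 |

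Both late visits fall after a waitlist course begun on that schedule, and treated waitlist patients are then 6 weeks nearer the end of their course than the EPN arm.

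**3. How many listed comparisons are touched** (section 2.8.3.2).
- Item 1: weeks 3, 18, 30 = 3.
- Items 2, 3 and 4: weeks 3, 6, 18, 30 = 3 × 4 = 12.
- Items 5 and 6: weeks 6, 18, 30 = 2 × 3 = 6.
- Item 7: weeks 3, 6, 18, 30 = 4.

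The total is 25, of which 7 × 2 = 14 are at weeks 18 and 30. Table 1 shows no Global Response Assessment at week 30; on that schedule the count is 13 of 24.

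**4. Size, as an illustration.** Uptake and late response rates are not given, so these are assumptions: the EPN arm stays at 55%, untreated waitlist patients stay at 28%, and a share c of the waitlist takes EPN and moves to 55%. Then

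waitlist response = 0.28 × (1 − c) + 0.55 × c, and difference = 0.27 × (1 − c).

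Power is for a two-sided 5% test with 49 per arm, by the normal approximation with pooled variance under the null. That is why it starts at 78% rather than 80%.

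| Uptake c | Waitlist response | Difference (points) | Power |
|---|---|---|---|
| 0% | 28.0% | 27.0 | 78% |
| 25% | 34.8% | 20.3 | 52% |
| 50% | 41.5% | 13.5 | 27% |
| 75% | 48.3% | 6.8 | 10% |
| 100% | 55.0% | 0 | 2.5% in the favourable direction |

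Under these assumptions the difference shrinks in direct proportion to uptake, although EPN works as well as the plan supposes and its effect persists in full.

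**The case against.** **The late arm comparisons are inferred.** The article never writes that the arms will be compared at weeks 18 and 30; the only comparison it ties to a visit is week 6. That is correct, and an analysis plan that is not shown may set out visit-by-visit methods. But outcomes 1 to 7 lack the arm restriction that items 8 and 9 carry, and the only tests named are two-sample tests. The point rests on that combination.

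**Randomisation still protects the contrast.** It does. Immediate EPN against delayed, optional EPN is a valid randomised comparison at every visit. A reader might call the late comparisons confounded, or conclude that between-arm P values there must be forbidden. The documents support neither; what lapses is the description as EPN versus no intervention.

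**EPN is offered, not given.** This stands too. Uptake is unknown, and with very low uptake the dilution would be slight.

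**A reader might infer that the sign would reverse.** If all 72% of waitlist non-responders took EPN and 55% of them responded, the waitlist would reach 0.28 + 0.72 × 0.55 = 67.6%, above 55%. The documents do not support this. The 55% is a whole-arm rate and already includes women who would have improved untreated. If EPN never prevents an untreated response (assumption), the rate among untreated non-responders is (0.55 − 0.28)/0.72 = 37.5%, and the waitlist reaches 0.28 + 0.72 × 0.375 = 55%, with no reversal. The 67.6% also needs full uptake, lasting response in every week-6 waitlist responder, and a reading of unresolved symptoms as a reduction below 50%, which section 2.8.2 does not state.

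**A reader might infer that the test is blind to durability.** The zero at full uptake arises because the EPN arm is held at 55%, which already assumes full durability. If that arm faded, the result would differ.

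**A reader might take lasting effect as a trial objective.** In the Discussion it is background on theory and earlier studies; the stated aims are effectiveness and safety.

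**Conclusion.** The point holds for weeks 18 and 30 only. Arm comparisons there do not estimate the stated contrast with no intervention, and a null result cannot be taken as loss of effect. They make up 14 of 25 listed secondary comparisons, or 13 of 24 by Table 1.

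The size depends on uptake, which the article does not give. On the assumptions above, the difference ranges from 27 points with no uptake to 0 with full uptake. If the EPN effect fades, the earlier course in the EPN arm would matter as well, but the documents give no rate of fading, so this is not sized.

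The primary outcome, the sample size and the week-3 and week-6 secondary outcomes all precede waitlist EPN and stand. This should be fixed, but it does not threaten the main result.

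**What to change.** In sections 2.8.3.2 and 2.9:

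- State that inference on EPN versus no intervention is limited to weeks 3 and 6.
- Report weeks 18 and 30 as durability within the EPN arm: change from baseline and maintenance of week-6 response, with 95% confidence intervals.
- Label any between-arm contrast at weeks 18 and 30 as immediate versus delayed, optional EPN, keep patients in the arm to which they were randomised, and say that a null result is not evidence of lost effect.
- Record which waitlist patients took EPN and on what dates. Describe them separately, timed from their own EPN start, rather than dropping them from their arm.
- Add the point to the limitations in the Discussion.

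The waitlist offer and the sample size need no change for this. The cost is wording and a record of uptake and dates. The small downside is giving up a randomised long-term claim against no intervention, which this design cannot support; the within-arm results that replace it cannot separate EPN from natural recovery and should be described so.

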### Recruitment strategies

2.2

Patients are planned to be recruited via advertisements in websites and posters from hospitals and communities. All potentially eligible women with hot flashes will be invited to the trial, continued with a series of history taking, questionnaire, HF diary, ultrasound of uterus and ovaries, and laboratory examination to screen and enroll the patients, as recommended by ACOG guideline.^[2]^ Eligible patients will be randomly divided into EPN group and waitlist control group.

Personal information including age, marriage, menstrual, education background, and medical history are cautiously recorded. Hot flashes diaries are applied to assess the severity of HF symptoms. Menopause rating scale (MRS) and Menopause-Specific Quality of Life Questionnaire (MENQOL) are applied to assess the influence on the quality of life. Patients’ expectance and confidence evaluation toward EPN will also be evaluated before the trial. The duration of the trial is 31 weeks for each patient, including 1-week baseline assessment (week 0–1), 6-week treatment period (week 1–6), and 24-week follow-up (week 7–30).

### Randomization and allocation concealment

2.3

Eligible patients will be randomized into the EPN group or the waitlist group in a 1:1 ratio with a variable block. Randomization sequence numbers will be produced by SAS 9.4 and kept in sealed opaque envelops. The envelops will be numbered and opened sequentially in accordance with the enrollment order.

### Blinding

2.4

The acupuncturists and patients in this trial cannot be blinded. Evaluators and statisticians will be assigned separately from the operators to ensure they are blinded to the group allocation.

### Participants

2.5

In total, 122 women patients with moderate to severe menopausal HF will be recruited in the trial.

### Inclusion criteria

2.6

Patients who fulfill all following criteria will be included.

1.Aged between 40 and 60 years old.2.Scoring 14 points or more^[13]^ in at least 1 day during the 1-week baseline assessment, or having an average of ≥ 7 moderate or severe heating per 24 hours^[8]^ recorded in HF Dairy.^[14,15]^3.Fulfilling either condition mentioned below:a.The last menstrual period was more than 12 months ago (including 12 months);b.In the late menopausal transition, and has amenorrhea for more than 60 days;c.Follicle-stimulating hormone ≥25IU, and has vasomotor symptoms of HF, sweating, insomnia, migraine, or restlessness, etc.4.Volunteer to participate in this study and sign the informed consent.

### Exclusion criteria

2.7

Patients who fulfill any of the following criteria will be excluded.

1.Usage of HRT via transdermal administration in the previous 1 month, or via oral or intrauterine administration in the previous 2 months; usage of phytoestrogen therapy, transvaginal estrogen administration, or estrogen or progesterone injection in the previous 3 months;2.Bilateral salpingo-oophorectomy;3.Amenorrhea secondary to premature ovarian failure, ovarian cysts or tumor, thyroid disease, hyperprolactinemia, or Cushing's syndrome, etc.;4.Accepted acupuncture or drugs to treat the symptoms of HF within the previous 3 months;5.Received radiotherapy or chemotherapy before;6.Coagulation dysfunction, or taking warfarin, heparin, and other anticoagulant drugs at present;7.Suffering from skin diseases, such as eczema, psoriasis, etc.;8.Severe hepatic and renal insufficiency;9.Uncontrolled hypertension, diabetes, or thyroid disease;10.Diabetic neuropathy and mental illness (including depression);11.Being pregnant, breastfeeding, or planning to be pregnant during the trial;12.Regular usage of sedatives or anti-anxiety drugs;13.Smoking for more than 5 years (at least 20 cigarettes a day on average),^[16]^ or with the problem of alcohol abuse;14.Installation of pacemakers;15.Poor compliance.

